#### Verbal and written consent for surrogates

Some patients’ surrogate decision-makers may live outside of the area (in a different state), or cannot come to the VA for in-person informed consent. Initially, a waiver of signed consent for surrogates was not approved. At this time, a signed written consent form is required prior to any surrogate interviews. To accomplish this, we mail a consent form to the surrogate, review the consent form and conduct consent verification over the phone. The surrogate is then given a stamped and addressed envelope to return the signed consent form. After consent is obtained, we can then call and schedule a phone or in-person interview. This is time consuming and can result in several (up to 10) attempts to contact the surrogate. Therefore, we now obtain a written consent waiver for surrogates. After calling a potential surrogate participant, if they answer all questions on the consent verification accurately within three tries, the surrogate can provide verbal consent over the phone, and we can continue with the study interview. If the surrogate is available in person, then a written informed consent form is reviewed and signed. All surrogates are still required to complete and return a signed HIPAA authorization by mail for their interview information to be used in the study.

### Intervention and control conditions

After the baseline interview, participants in the PREPARE arm review the PREPARE website (www.prepareforyourcare.org) in the research offices. Research staff are available to answer questions, but participants are asked to go through the PREPARE website (Steps 1 through 5) on their own and in its entirety. As participants progress through the website, PREPARE asks questions about overall life values and goals for medical care. At the end of the program, the participant is asked to make an action plan to do one ACP task in the next weeks to months. At the end of the interview, research staff print out the action plan and a summary of the Veteran’s medical wishes and compile this into a folder that also contains the PREPARE pamphlet, booklet, DVD, and the log-in code to the website. The PREPARE DVD contains the same information found on the website, but without interactive or tailored functionality. PREPARE arm participants are also given an easy-to-read advance directive to review and take home (http://www.iha4health.org/our-services/advance-directive/) [13]. Participants in the control arm are only given the advance directive, are asked to review it for at least 10 minutes and to take it home. The control arm is not given any information about the PREPARE materials. One to 3 days before the Veteran’s next scheduled primary care appointment, research staff call the PREPARE arm participants to remind them to bring in their action plan, summary of wishes and advance directive to their doctor’s appointment. For the control arm, research staff members only remind Veterans about their upcoming primary care appointment.

### Randomization procedures

We block randomize Veterans based on limited health literacy, as determined by a validated question concerning confidence with medical forms [30], and non-white race/ethnicity to ensure these variables are equally distributed between randomization groups. A statistician not involved in recruitment or data collection used a computer-based random number generator to create a randomization scheme within four groups (high health literacy and white race/ethnicity, high health literacy and non-white race/ethnicity, low health literacy and white race/ethnicity, and low health literacy and non-white race/ethnicity) in random block sizes of 4, 6, and 8. This randomization scheme was imported into the Research Electronic Data Capture (REDCap) software by the statistician. Only the research personnel who conducted the baseline interview use this software prior to the baseline interview to determine which study arm the Veteran is assigned to and which ACP interventions (PREPARE versus control) to give the enrolled participant. Randomization information is kept separate from other research or identifying Veteran data and is only associated with a unique Veteran identification number.

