### Overview of study procedures

Veteran recruitment occurs in waves to target upcoming primary care clinic appointments and to allow time for recruitment and scheduling of a baseline interview (Fig. 1, Study Flowchart). Veterans are then randomized to the PREPARE arm (PREPARE website [15], action plan creation within the website, and provision of PREPARE logins and PREPARE materials in pamphlet, booklet and DVD formats to take home) plus an easy-to-read advance directive [12], or the control arm which only receives the easy-to-read advance directive. Outcomes pertaining to ACP engagement behavior are assessed at 1 week, 3 months, and 6 months between the two study arms (Table 2).

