### Blinding

Participants are blinded to group assignment. They are told that the purpose of the study is to help patients make difficult medical decisions, and that each participant would review one of two guides. This blinding is enhanced by each group obtaining some form of ACP materials, such as the easy-to-read advance directive. To ensure blinding of research staff for all follow-up outcome assessments, staff who had completed the baseline interview and randomization for a given participant will not conduct any follow-up interviews with that participant.

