#### Measures related to ACP engagement including behavior change process measures and ACP actions

Full ACP engagement is measured by Veteran self-report at baseline, 1 week, 3 months, and 6 months. Based on Social Cognitive Theory and Behavioral Change Theory [18, 19], we included measures to capture theoretical constructs related to contemplation of behavior, planning or intention to act on the behavior, and the behavior itself. If only the action behavior is measured, such as completion of an advance directive, clinically significant movement along the behavior change pathway will be missed. Thus, it is important to ascertain ACP process measures of behavior change (knowledge, contemplation, self-efficacy, and readiness) for several ACP actions in addition to whether they have completed an ACP behavior (Action Measures). These actions include 1) identifying of a surrogate, 2) identifying values and goals, 3) choosing the level of leeway or flexibility in decision-making for the surrogate, 4) and communicating this information with clinicians and surrogate decision makers, and 5) documenting one’s wishes [22]. As Veterans may have had varying degrees of experience with ACP, we assess baseline engagement in ACP within the past 5 years (standardized based on pilot data). We also ask about engagement in ACP since the randomization date, for example, “Within the past one week, 3 or 6 months”, depending upon the follow-up interval.

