### Data analysis

#### RCT efficacy analysis

Our primary analyses will compare advance directive completion rates and change in engagement in the five ACP behaviors (see Primary outcome section) using behavior change measure scores on a 5-point Likert scale (analyzed as average Likert scores and total scores of 57 to 285) and action measure scores using yes and no responses (scores 0 to 25) from baseline to 1 week, and 3, and 6 months between study arms. We first will use means, medians, and ranges to describe continuous variables, and we will use proportions to describe categorical and dichotomous variables. Baseline comparability of the two groups will then be assessed using t-tests for continuous variables and chi-square tests for proportions. To examine the outcomes between the two study arms longitudinally, we will use mixed effects linear, Poisson, or negative binomial regression for continuous outcome measures and mixed effects logistic regression for dichotomous measures. The mixed effects models will include a random effect for subjects and fixed effects for the primary modeling terms of time, study arm, and an interaction term of study arm and time. We will treat the time variable in three different ways: (i) our first model will encode the time variable as a dummy variable for baseline versus the post-intervention time points; (ii) we will next model time in a continuous linear fashion; (iii) we will lastly consider an arbitrary time course by treating time as a categorical factor variable. We will also adjust for the randomization blocking factors of health literacy (limited versus adequate) and race (white versus non-white) [39] and for any predictor variables that differ between study arms at baseline. We will also include random physician intercepts to account for nesting of patients within physicians. We will consider including random effects for the primary modeling terms of time, study arm, and their interaction. Modeling decisions (for example, which mean structure to use and which random effects to include) will be based on comparing values of the Akaike Information Criterion. Models will be fit using the xt routines in Stata. Mediation analyses will use Stata’s mediation package, which allows estimation of the average causal mediation effect using a potential outcomes framework with either continuous or binary outcomes and allows for sensitivity analyses with respect to violation of the sequential ignorability assumption [40]. Moderating variables will be tested with interaction terms.

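### The baseline interviewer opens the arm assignment before the interview, so the self-reported engagement scores that anchor the change analyses are collected by someone who knows the arm

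*Protocol article*

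**What the plan says.** Randomization procedures gives the order explicitly. It says that the baseline interviewers, and only they, "use this software prior to the baseline interview to determine which study arm the Veteran is assigned to". The look-up and the interview are done by the same person, and the look-up comes first.

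Intervention and control conditions places delivery later: "After the baseline interview, participants in the PREPARE arm review the PREPARE website".

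Blinding contains two statements. For Veterans: "Participants are blinded to group assignment". For staff, the safeguard is limited to later contacts: "To ensure blinding of research staff for all follow-up outcome assessments", whoever did a Veteran's baseline interview and randomization does not interview that Veteran again. Nothing is said about keeping the interviewer unaware of the arm at baseline.

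The exposed data come from the ACP Engagement Survey: "Full ACP engagement is measured by Veteran self-report at baseline, 1 week, 3 months, and 6 months". Table 2 lists this survey under primary outcome variables. RCT efficacy analysis includes change in engagement from baseline in its primary analyses and fits mixed models with "an interaction term of study arm and time", the first of which contrasts baseline with all post-intervention time points.

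**The concern.** In these models baseline is an outcome time point, and the treatment effect is the between-arm difference in departure from it. If knowing the arm changes how an interviewer presents, clarifies or records baseline answers, the between-arm shift passes into the effect estimate with opposite sign. Baseline scores recorded lower in the PREPARE arm would look like a larger gain.

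Randomization does not protect against this, because the measurement follows the disclosure of the arm. The article's own rule that baseline staff may not do follow-up interviews shows that interviewer knowledge was regarded as a threat. The same survey is left without that protection at its first administration. What is at stake is the credibility of the engagement results, which the article calls just as clinically meaningful as the documentation outcome.

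**Working it through.** **1. Order of events.**

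| Section | What it fixes |
|---|---|
| Table 2, Screener column | Race/ethnicity and the health literacy question, the two stratifiers, are available before the baseline interview, so an early look-up is feasible |
| Randomization procedures | Arm looked up before the baseline interview, by the interviewer |
| Intervention and control conditions | Arm first needed after the baseline interview |
| Blinding | Staff safeguard at follow-up only |
| Logistic challenges (Discussion) | Baseline and randomization named together, order not fixed |

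Only one section fixes the order, and no other section reverses it.

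**2. The plan's own figure.** Secondary outcomes gives an SD of 10, 175 per arm, and 80% power for a 3-point difference. SE = 10 × √(2/175) = 1.069. Power = Φ(3/1.069 − 1.96) = Φ(0.846) = 80.1%. The figure reproduces and does not change under this point.

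**3. How a baseline shift enters.** Let b be the between-arm shift in recorded baseline scores caused by knowledge of the arm.

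- Baseline-versus-post dummy, or categorical time: the bias in the arm-by-time contrast is −b.
- Linear time: smaller. With complete data at 0, 0.25, 3 and 6 months, mean time is 2.3125 and the sum of squared deviations is 23.67. A 1-point baseline shift changes the slope by 2.3125/23.67 = 0.0977 per month, so the fitted change to 6 months moves by 6 × 0.0977 = 0.59 points.

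**4. Illustration for the baseline-versus-post contrast, no true effect.** Type I error = 1 − Φ(1.96 − b/SE) + Φ(−1.96 − b/SE), with SE = SD of change × √(2/175). The article gives neither b nor the SD of change; both are assumed.

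| b (points) | SD 8 | SD 10 | SD 12 |
|---|---|---|---|
| 0 | 5.0% | 5.0% | 5.0% |
| 0.5 | 9.0% | 7.5% | 6.8% |
| 1 | 21.5% | 15.5% | 12.2% |

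Only b/SD matters. At SD 10 the two shifts are 0.05 and 0.1 SD, so the result can be read on any score scale.

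**5. Precision of an analysis without baseline scores.** If scores have equal variance over time and correlation ρ between baseline and follow-up, SD of change = SD × √(2(1 − ρ)). The SE of a follow-up-only contrast relative to a change contrast is then 1/√(2(1 − ρ)). At an assumed ρ of 0.5 the ratio is 1.00. At 0.70, the 7-day test-retest value for the process measures, it is 1/√0.60 = 1.29. The power in step 2 uses the SD of the score itself, so it already describes a comparison that does not use baseline.

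**The case against.** The strongest reply is that the interviewer has little room to influence these data. Engagement is self-reported on Likert and yes/no items by Veterans described as blinded. Interviews follow standardised scripts, staff are signed off before working alone, and a 10% random sample of interviews is observed. This stands as mitigation and makes a large shift less likely. It does not blind the interviewer.

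Advance directive documentation, on which the trial was sized, is read from the medical record and is not reached by this route. That stands in full. Items collected at screening are also outside the point.

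Three stronger readings are tempting and not supported:

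- *That the article contradicts itself on the order.* Overview of study procedures says "Veterans are then randomized to the PREPARE arm", which a reader might take as after the baseline interview. The preceding sentence speaks only of allowing time to schedule that interview, which is compatible with the stated look-up order.
- *That early disclosure allowed selective enrolment.* The look-up is described as deciding what to give an enrolled participant, and screening is a separate step. The article does not say whether the consent teach-back comes before the look-up. That is an ambiguity and no evidence of selection.
- *That the bias amounts to a third of the detectable difference.* A reader might set a 1-point shift against the 3-point target. No section supports a shift of that size. The SD of 10 also belongs to a 57-point score, whereas RCT efficacy analysis uses average Likert scores, totals of 57 to 285 and action scores of 0 to 25. Under linear time the shift is not carried over in full.

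**Conclusion.** The point holds for the self-reported engagement outcomes. As written, the procedure exposes their baseline values to interviewer bias without need, and nothing else in the article removes that exposure. It is a risk and has not been shown to have occurred; its size and direction are unknown. The figures of 7.5% to 15.5% for a shift of 0.5 to 1 point rest on an assumed shift, an assumed SD of change of 10, 175 per arm, a normal approximation, and the baseline-versus-post form of the model. No stated sample size or power figure changes. This should be fixed, but it does not threaten the documentation outcome. If the sentence in Randomization procedures simply misdescribes practice, correcting it settles the matter.

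**What to change.** 1. In Randomization procedures, correct the order if the sentence is wrong. If it is right, amend the procedure so that REDCap releases the assignment only after the baseline instruments are completed and locked. This costs one sentence and a form-order setting. It cannot help the present cohort, because Trial status reports that all 410 Veterans have been recruited.
2. For the enrolled Veterans, report the order actually followed, using REDCap timestamps where they exist. Interviews first recorded on paper and entered later may have no usable timestamp; their number should be given.
3. Add a sensitivity analysis that compares follow-up engagement scores between arms, adjusted for the randomization strata (health literacy and race/ethnicity) and without the interviewer-collected baseline survey values. Randomization and the blinded follow-up interviewers protect this contrast. It needs no new data. The cost is some precision: under the assumptions in the working, an SE up to about 1.29 times that of a change contrast at a correlation of 0.70, and none at 0.5.
4. If the sensitivity result differs materially from the change-from-baseline result, say so when the engagement findings are interpreted.

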### Blinding

Participants are blinded to group assignment. They are told that the purpose of the study is to help patients make difficult medical decisions, and that each participant would review one of two guides. This blinding is enhanced by each group obtaining some form of ACP materials, such as the easy-to-read advance directive. To ensure blinding of research staff for all follow-up outcome assessments, staff who had completed the baseline interview and randomization for a given participant will not conduct any follow-up interviews with that participant.

### Intervention fidelity

A study protocol manual was created for research staff, and several training sessions have been and will continue to be conducted until the end of the study. In addition, we have created standardized study scripts for recruitment and interviewing and have created training videos to standardize the study procedures. Checklists for all follow-up assessments have also been created. All staff being trained need to learn each item on the checklist, shadow other study staff, and be evaluated by their supervisors for each checklist item. Study staff cannot conduct PREPARE study tasks independently until they can demonstrate mastery of each checklist item. After study staff members are considered independent to conduct study tasks and interviews, a 10 % random sample of interviews will be observed to ensure fidelity to study procedures. Data collection initially began with paper surveys that were entered into a REDCap survey capture database. At least 50 % of the data entry was reviewed by an independent staff member to ensure data were entered correctly. Part way through our study, we switched to live data capture through REDCap. This allows us to streamline our data entry procedures and reduce the use of printed paper surveys. To reduce missing data, automatic prompts have been created within the REDCap program that will not allow study staff to progress if a question is left blank. Concerns about question wording or response option interpretation are reviewed at regular team meetings.

### Ethics

This study has been approved by the University of California, San Francisco (UCSF) and the San Francisco VA Medical Center institutional review boards (UCSF IRB reference # 10-00098) and is registered at ClinicalTrials.gov (NCT01550731). This study is funded by the United States Veterans Administration, Health Services Research and Development.

### Measures and data collection

A range of measures are collected to capture the full process of ACP and whether the PREPARE intervention has any effect on ACP, medical decision-making, patient activation, clinician responsiveness, and doctor-patient communication. Table 2 lists all study measures assessed at multiple time points. Details of the main outcome measures are described below.

**Table 2 Tab2:** Constructs and measures for evaluating the efficacy of the PREPARE Study

Construct	Measure	# items	Reliability/validity	Screener	Baseline	1 week	3 month	6 month
	Eligibility screening variables							
Cognitive impairment	Short Portable Mental Status Questionnaire (SPMSQ)	7	Sensitivity 86.2 %, specificity 99.0 % [43]	X				
	0 to 2 = eligible							
	3 to 7 moderate impairment (go on to the Mini Cog three-item recall)							
	≥8 severe impairment = ineligible							
Cognitive impairment (participants scoring 3 to 7 errors on the SPMSQ)	Mini Cog (three-item recall as needed, if SPMSQ screen + for cognitive impairment)	3	Sensitivity 76 %, specificity 89 % [44]	X				
	If recall ≥ two words = eligible							
Vision	Ability to see words on a newspaper [42]	1						
	Moderator variables							
Demographic information	Age, gender, race/ethnicity [45], income, marital status, and education			X	X			
Health literacy screen	“How comfortable are you filling out medical forms by yourself?”	1	AUROC 0.80 (95 % CI = 0.67.0.93) for inadequate health literacy [46]	X				
	“Qué tan seguro (a) se siente al llenar formas usted solo (a)”							
Health literacy assessment	Short form Test of Functional Health Literacy in Adults s-TOFHLA, scores 0 to 36) [47] Continuous & dichotomized to limited = 0 to 22 and adequate = 23 to 36	36	Cronbach’s α = .97		X			
			Correlation coefficient w/ other literacy tests > 0.80 [47]					
United States acculturation	Based on Acculturation scale (USAS) “How many years have you lived in the U.S.?”	1	Cronbach’s α = .98		X			
			Associated w/ desire to know prognosis [48]					
Finances	“In general, how do your finances usually work out at the end of the month?”	1	Associated with functional impairment and comorbidity [49]		X			
Socioeconomic status and social standing	Social standing ladder (that is, place an “x” where you think you stand relative to other people in society)	1	Associated with functional decline [50]		X			
Functional status	Activities of Daily Living (ADL) and Instrumental Activities of Daily Living (IADL)	15	Morbidity/mortality correlation [51, 52]		X			
Self-rated health status	In general how would you rate your health? (5-pt Likert)	1	Correlation with global health, spearman’s rho = -63, and mortality [53]	X				
Self-rated quality of life	In general, how would you rate your overall quality of life in the past week (5-pt Likert)	1	Test-retest coefficient = 0.81 [54]	X				
Comorbid illness	Determined by ICD-9 codes (chart)	0	Mortality c-stat: [23]		X			
	Charlson comorbidity score [24]		Charlson = 0.704					
	Elixhauser comorbidity score [55]		Elixhauser = 0.793					
Social support	Modified Medical Outcomes Study Social Support (mMOS-SS)	11	Cronbach’s α = 0.88-.93 [56]		X			
Religion/spirituality	Self-reported extent of how spiritual/religious (5-pt Likert) and role play in decision-making.	4	Spirituality associated with quality of life. Religiosity associated with wanting all measures to extend life [57]		X			
Prior ACP experience	Prior ACP experiences (for example, Ever had to make life threatening medical decisions?”) [12]	5			X			
Major life changes	For example, “In the past 6 months, have you or someone close to you been faced with a serious medical problem or diagnosis?”	4						X
	Mediator variables^a^ (also measured as Outcome Variables)							
Baseline knowledge	Knowledge subscales of the ACP Engagement Survey.	6	Cronbach’s α = 0.84 (0.76-0.90), ICC = 0.70 (0.50-0.82) [15]		X			
Baseline self-efficacy	Self-efficacy subscales of the ACP Engagement Survey.	6	Cronbach’s α = 0.83 (0.75-0.89), ICC = 0.60 (0.41-0.76) [15]		X			
Baseline readiness	Readiness subscales of the ACP Engagement Survey.	10	Cronbach’s α = 0.92 (0.88-0.95), ICC = 0.60 (0.53-0.81) [15]		X			
Baseline barriers	Checkbox of 13 common barriers	13	Associated with ACP [25]		X			
Baseline attitudes	Processes of Change for ACP [16]	34	Responsive to an ACP intervention [15]		X			
Desired role in decision-making	Control Preference Scale (CPS) [58]	2	Correlation between preferred and actual role in decision-making [59–61]		X			X
	Primary Outcome Variables							
Full process of ACP	ACP Engagement Survey: Process Measures of knowledge, contemplation, self-efficacy, readiness	116	Process Measures: Cronbach’s α = 0.94 (0.91-0.96), ICC = 0.70 (0.54-0.82) [15]		X	X	X	X
	Action Measures: completion of advance directives, discussions		Action Measures: ICC = 0.87 (0.79-0.92) [15]					
	Secondary outcome variables							
Communication quality	Modified CAHPS (that is, did this provider explain things in a way that was easy to understand?)	14	Comparative Fit Index = 0.98, Tucker Lewis Index = 0.98		X	X		
			Internal consistency: 0.58 to 0.92. ≥ 0.70 for four of eight constructs [62]					
Satisfaction with communication	For example, “How satisfied are you that you could share your most important concerns with X/that X understood what was most important to you?)	8			X	X	X	X
Satisfaction with care	Care Consistent with Goals: Comparison of 10-point ratings about aggressiveness of care desired and care currently receiving.	4			X			X
Barriers to ACP	Checkbox of 13 common barriers (for example, thinking about the topic makes me nervous or sad; I am too healthy; I am too busy; my family or doctor is too busy; I prefer to leave my health in God’s hands; I don’t want to burden my family and friends; I want to leave the choice to my friends and family; I want to leave the choice to my doctors; and an open-category response for “other.”)	13	Associated with ACP [25]		X			X
Attitudes about ACP	Processes of change for ACP [16]	34	Responsive to ACP intervention [15]		X			
Desired role in decision-making	Control Preference Scale (CPS) [58]	2	Correlation between preferred and actual role in decision-making [59–61]		X			X
Satisfaction with decision making	Decisional Conflict Scale	20	test-retest coefficient = 0.81			X	X	X
			α coefficient: 0.78-0.92 for total scale. 0.58-0.92 for subscales [31]					
Depression and anxiety	Patient Health Questionnaire (PHQ-4)	4	Cronbach’s α = 0.78 [63]		X	X	X	X
Surrogate reports of patient engagement in ACP and other surrogate items	Modified from the ACP Engagement Survey [22], (for example, “Did [Veteran] ask you to be their surrogate decision maker, talk to you about leeway, talk to you about their values, tell other family or friends about their wishes, ask clinicians questions or have you ask clinicians questions?”	45						X
	Prior ACP	6						
	Care consistent with goals	4						
	Decisional Conflict	19						
	Implementation	13						
Implementation: acceptability	Acceptability and Usability		1 factor explained 81-85 % of variance/scale. Kuder-Richardson >0.75 [12]		X			
	(a) Ease of use and understanding	8						
	(b) Usefulness in decisions & discussions	6						
	(c) Attitudes about norms or expectations	6						
	for example, “Did you try to fill out the advance directive we gave you?” “Did you give it to a medical provider, social worker, or case manager?” If they respond no, “Why do you think you did not turn it in?” “What can we do to get other people to look over these materials?” “What would motivate them?” “What suggestions do you have to make these materials better?”							
Implementation: feasibility	Feasibility (Control) (for example, when and where to review ACP materials)	7						X
	Feasibility (PREPARE only) (for example, when and where to review ACP materials, and which PREPARE materials did you use and would recommend)	34						
	“Do you remember what your action plan was?”							
	“Did you complete your action plan?”							
	If no to completing an action plan, “Why do you think you have not completed your action plan?”							
	“After the first study visit, did you look at the (action plan, summary of your wishes, the PREPARE website, pamphlet, Booklet/or DVD) again?							
	If no, “Why do you think you didn’t you look at it?”							
	Satisfaction questions include “Which of the PREPARE materials was the most helpful?”; “Which would you use again?” “Which did you share with your decision maker, friends, or family?” “When is the best time to see the PREPARE materials?” “Where do you think most people would prefer to review the PREPARE materials (home, clinic, or public space)?							

^a^Whereas the mediator variables, measured at baseline, may explain how or why a particular effect or relationship occurs, these variables may also be affected by the intervention and are therefore also measured as outcome variables

